## Abstract

**Background:**

The clinical environment in which health care providers have to work everyday is highly complex; this increases the risk for the occurrence of unintended events. The aim of this randomised controlled trial is to improve patient safety for a vulnerable group of patients that have to go through a complex care chain, namely elderly hip fracture patients.

**Methods/design:**

A randomised controlled trial that consists of three interventions; these will be implemented in three surgical wards in Dutch hospitals. One surgical ward in another hospital will be the control group. The first intervention is aimed at improving communication between care providers using the SBAR communication tool. The second intervention is directed at stimulating the role of the patient within the care process with a patient safety card. The third intervention consists of a leaflet for patients with information on the most common complications for the period after discharge. The primary outcome measures in this study are the incidence of complications and adverse events, mortality rate within six months after discharge and functional mobility six months after discharge. Secondary outcome measures are length of hospital stay, quality and completeness of information transfer and patient satisfaction with the instruments.

**Discussion:**

The results will give insight into the nature and scale of complications and adverse events that occur in elderly hip fracture patients. Also, the implementation of three interventions aimed at improving the communication and information transfer provides valuable possibilities for improving patient safety in this increasing patient group. This study combines the use of three interventions, which is an innovative aspect of the study.

**Trial registration:**

The Netherlands National Trial Register NTR1562

## Background

In many Western countries the population is ageing rapidly. This change in population demographics makes the necessary adjustments in healthcare needs and requirements for this group an increasingly important issue in research and policy [1]. Besides the expected shortages in healthcare staff, the specific clinical challenges that have to be dealt with in elderly patients are important. Elderly patients often do not show typical signs and symptoms of a disease, thus making a timely and accurate diagnosis more difficult [2]. In addition, these patients are often suffering from substantial co-morbidity, which further complicates the treatment.

In accordance with the changing demographics of the general population, the incidence of hip fractures will also increase in the upcoming years [3]. Hip fracture patients represent a clinical management challenge; they are an increasing group of predominantly older persons with a variety of medical co-morbidities under varying levels of control. In addition, they are facing operative repair of the fracture and frequently a difficult postoperative rehabilitation [4]. Even after this long rehabilitation, only half of these patients will return to their community and only about a third regains their former level of function [5,6]. Research has shown that hip-fractures are associated with an one-year mortality as high as 14 to 36% [6]. Also, the treatment of a hip fracture is very expensive [7].

The care process for hip fracture patients has been classified as highly complex. To illustrate the multidisciplinary treatment; a case study in a university hospital in Sweden showed that hip fracture patients initially meet doctors, nurses and other staff in the Emergency Department (ED), radiology, surgery, geriatrics, anaesthesiology, the operating room, and sometimes the Intensive Care Unit (ICU) [8]. The involvement of many different specialties makes optimal communication, hand-offs and information transfer even more important. To minimise the risk of complications, a complex series of interventions is required, several physician specialties and hospital departments need to be coordinated, and time is of the essence. Unfortunately, this level of coordination seems difficult to achieve [4]. Structuring the information transfer and communication can be an important step in this process.

The study we describe in this protocol focuses on the effects of improving the quality and safety of hip fracture patients by structuring the information transfer and interprofessional communication. An intervention study is set up to implement three interventions in a combined manner and is aimed at 1) improving the clinical communication between care providers with the introduction of the SBAR-communication tool, 2) strengthening the role of patients and their families with a patient safety pocket card and 3) providing patients and their families with specified information for the period after discharge by handing out a leaflet which describes the most common complications and who to contact with specific questions. One of the goals of this study is to establish whether this combined intervention programme can result in a reduction of the complication and adverse event (AE) rate in elderly hip fracture patients.

A complication is an unintended and unwanted event or state during or following medical specialist treatment, that has an unfavourable effect on the health of the patient to such an extend that adjustment of the medical treatment is necessary or that irreparable harm has occurred [9]. An Adverse Event (AE) is defined as an unintended injury that results in temporary or permanent disability, death or prolonged hospital stay, and is caused by healthcare management rather than by the patient's underlying disease process [10-13]. De Vries et al. (2008) recently conducted a systematic review based on eight patient record review studies to calculate the mean overall incidence of in-hospital AEs. They stated that in 9.2% of all hospital admissions one or more AEs occurred. Of these AEs nearly half (43.5%) were preventable and 7.4% contributed to death [14]. Other research showed that elderly patients are at increased risk of suffering from Adverse AEs [15,16]. To our knowledge, there is no published material on the AE rate in elderly hip fracture patients yet.

AEs are generally caused by a combination of factors. These often involve organisational, human, technical and patient-related factors [17,18]. One of the contributing human-related factors are communication failures [19], they are estimated to be of major influence in 60-70% of serious incidents [20-22]. There are many barriers that can potentially contribute to communication difficulties between clinicians. Some examples are: a lack of structure, differences in communication styles and uncertainty about who is responsible for the patient's care [23-25]. Several tools have been developed to structure the communication between care providers. One of these is called SBAR, a situational briefing tool developed by Kaiser Permanente [19,24]. SBAR stands for Situation, Background, Assessment, Recommendation and serves as a model that care providers can use to structure clinical communication. So far, to our knowledge, only a limited amount of published work exists on the effectiveness of the SBAR-tool on improving clinical communication [22,24]. The SBAR-tool could have the potential to improve communication between care providers about patients when effective in the clinical setting, so further evidence is needed. This can benefit the care for our complex patient group where a timely and accurate transfer of information is essential.

Another important factor for patient safety is improving the communication between care-providers and patients. Previous findings provide some support for the view that patients are willing to be more involved when it comes to reducing patient safety incidents [26]. However, some research has also shown that this need for patient involvement varies for several demographic variables, such as age. Younger patients tend to want more involvement than older patients. [26-29]. It can therefore be useful to stimulate elderly patients to get more actively involved in their own care process as they are the only one to be involved in the care process from beginning to end. Of course, an important question is to what extend elderly patients actually want to be involved and whether they feel comfortable enough to actively question the (safety) practices of health care staff. It is also important that patients should never feel responsible for the safety of the care they receive.

A third issue related to the previous two is the lack of information that patients can experience, especially during and after discharge. Smit et al. (2005) showed that patients, in their own opinion, do not receive enough information on what they have to do in an emergency situation, how to use several medications together and what they are allowed to do after discharge [30]. Often, patients are discharged from hospital and come back to the outpatient clinic after a scheduled amount of time. In between, it is not always clear to them who to turn to with questions following the hospital admission. An adequate and timely transfer of information about the hospital admission towards the general practitioner (GP) is sometimes lacking so the GP is not completely informed about the current medical condition of the patient [31,32]. This lack of information transfer can make it difficult to contact the appropriate care provider with specific questions, even though early detection and treatment of possible problems are very important.

### Aim and research questions

The aim of this randomised controlled trial (RCT) is to evaluate the effectiveness of a patient safety intervention programme for elderly hip fracture patients. Therefore, the following research questions will be addressed:

1. What is the nature and scale of adverse events and avoidable harm in the care chain for elderly hip fracture patients?

2. How is it, in the total care chain of elderly hip fracture patients, possible to reduce risks and unintended harm, and to ensure that complex care processes proceed more safely? This research question is divided into sub-questions for the three interventions:

a What is the effectiveness of the SBAR communication tool on unintended events and avoidable harm during hospital stay? (Intervention A)

b What is the effectiveness of a patient safety card with guidelines for patients and their families on signalling errors and patient trust in health care? (Intervention B)

c What is the effectiveness of evidence based bundles with regard to unintended events in the period after discharge? (Intervention C)

## Methods/Design

### Study design

This RCT is set up as a multi-centre intervention study in which hip fracture patients aged 65 years and older will be included. Surgical wards of three hospitals will participate in the intervention groups; one surgical ward in another hospital will serve as a control group. The patients in the control group receive care as usual. A baseline measurement using a retrospective record review study will be conducted. In the following RCT the effects of three different interventions will be compared to usual care, randomisation is at patient level. Within the three intervention wards patients are randomly assigned to one of four intervention groups. The groups will receive the following interventions:

• Group 1: use of SBAR communication tool for nurses in the surgical wards

• Group 2: SBAR and patient safety card

• Group 3: SBAR and information leaflet (bundles) for after discharge

• Group 4: SBAR, patient safety card and information leaflet (bundles) for after discharge

During the study period the morning rounds will be observed once a month in each intervention ward to look at the information transfer and communication between care providers. Two weeks and six months after discharge patients will be interviewed about their recovery and the added value of the interventions. Six months after discharge the records of the included patients will be reviewed to detect possible adverse events and unintended harm. Figure 1 gives an overview of the inclusion and data collection.

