### Participating surgical wards

Because the researchers will frequently have to visit the participating surgical wards during the study, one hospital region in the Netherlands will be chosen for the recruitment. Although the treatment for hip fractures is fairly standardised by means of protocols, we aim to include a surgical ward of each of the three hospital types that exist in the Netherlands; a university, a tertiary medical teaching and a general hospital. A fourth surgical ward in another hospital will be included as a control group. An inclusion criterion for the surgical wards is that they have to treat at least 100 elderly patients with a hip fracture each year. The wards will be recruited by informing already existing contacts within the wards about the study. If the ward agrees to participate an official intake by the researchers will follow. The nurses in the participating wards will be informed about the study during a meeting. In this meeting the interventions and the inclusion process will be explained. For each ward background information will be gathered about the number of patients, treatment procedures and discharge planning. This will make it possible to compare the wards and correct for important differences.

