### Randomisation

In this study surgical wards in three different intervention hospitals and one surgical ward in a control hospital will participate. The eligible patients in the intervention wards will be randomly assigned to one of four intervention groups. Since the SBAR tool cannot be randomised on patient level due to practical reasons, this intervention will concern all patients in the intervention wards. Before the start of the inclusion all Informed Consent Forms and intervention materials will be assigned a unique study number. The study numbers are equally divided over four intervention groups, to ensure equal group sizes as much as possible. All materials for each individual number will be gathered and put into an envelope; the stack of envelopes will be kept in the ward in consecutive order of the study numbers. Each time an eligible patient can be asked to participate, the first envelope of the stack will be used. The process of randomisation is also shown in Figure 2.

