### Data analysis

The data will be analysed using Stata 10.1 for Windows. During the data collection regular data checks (identify out-of-range answers, inconsistent responses and missing data) will be performed.

In the evaluation of the effectiveness of the intervention programme all analyses will be performed at patient and group level. The data will be analysed using the intention-to-treat principle. This means that patients will remain in the group to which they were randomly allocated at baseline. The patient characteristics will be compared for all groups and, if necessary, we will correct for differences.

The determination of complications is based on the complication registration of the Dutch Society of Medical Specialists (in Dutch: Orde van Medisch Specialisten). The determination of adverse events is based on three criteria; 1) an unintended (physical and/or mental) injury which 2) results in temporary or permanent disability, death or prolongation of hospital stay, and is 3) caused by health care management rather than the patient's disease. To determine whether the injury is caused by health care a six-point scale will be used, causation scores of 4-6 will be classified as adverse events. The preventability of the adverse events will also be measured on a six-point scale, scores of 4-6 will be classified as preventable adverse events. The incidence and mean number of complications and adverse events will be calculated.

The inter-rater reliability of the review process will be expressed as a kappa statistic. This kappa statistic will be calculated for the determination of the presence or absence of complications and adverse events. The records from the reliability study will be used for this analysis, they represent up to 10% of all reviewed patient records.

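### Only the card and leaflet contrasts are randomised; SBAR and programme versus usual care are confounded with hospital but described as a patient-level randomised comparison

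*Protocol article*

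**What the plan says.** All references are to the protocol article.

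- **Who is randomised.** Study design: "Within the three intervention wards patients are randomly assigned to one of four intervention groups". The four groups are SBAR alone, SBAR plus card, SBAR plus leaflet, and SBAR plus both.
- **SBAR is not randomised.** Randomisation: "Since the SBAR tool cannot be randomised on patient level due to practical reasons, this intervention will concern all patients in the intervention wards".
- **Where usual care is found.** Study design: "Surgical wards of three hospitals will participate in the intervention groups; one surgical ward in another hospital will serve as a control group", and "The patients in the control group receive care as usual". Participating surgical wards says that wards are recruited through existing contacts; no chance selection of the control ward is described.
- **How the comparison is presented.** Study design: "In the following RCT the effects of three different interventions will be compared to usual care, randomisation is at patient level". Aim and research questions describes a randomised trial of the programme, and question 2a asks for the effect of SBAR on unintended events and avoidable harm.
- **Handling of ward differences.** Participating surgical wards, on the background data gathered for each ward: "This will make it possible to compare the wards and correct for important differences".
- **Intention to treat.** Data analysis: "This means that patients will remain in the group to which they were randomly allocated at baseline".
- **Baseline.** A 2007 record review is planned in each hospital. The sections on the baseline measurement, on evaluation of the card and on general data collection use it, or the second review, as the reference for judging change.

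**The concern.** A reader of the Study design section would take the usual-care comparison to be protected by patient-level randomisation. It is not. Every randomised patient receives SBAR, and every concurrent usual-care patient lies in one ward of a fourth hospital. Anything that differs between that hospital and the other three enters the contrast together with the intervention: case-mix, surgical practice, discharge arrangements, record keeping, or the monthly observation of rounds, which is planned in the intervention wards only.

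At stake are question 2a and the effect of the programme against usual care. The trial contains no randomised evidence on either. The limitations section does not disclose this: it treats randomisation only as possible contamination between room-mates. The strengths section credits randomisation with reducing differences among the three intervention wards and is silent on the control ward.

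**Working it through.** **1. The plan's own figure.** Power calculation gives a difference of 5, SD 10, alpha 0.05, power 80%, 64 per group including the control group, raised to 80.

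- n = 2 × (1.960 + 0.842)² × 10² / 5² = 62.8, so 63 by the normal approximation. The two-sample t-test version gives 63.8, so 64.
- 64 / 0.80 = 80, which corresponds to 20% drop-out.

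The figure reproduces. The formula treats all patients as independent and has no hospital term, although the control group is a single hospital.

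**2. Which contrasts are randomised.**

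| Contrast | Allocation | Confounded with hospital? |
|---|---|---|
| Card v no card, among groups 1-4 | Randomised within wards | No |
| Leaflet v no leaflet, among groups 1-4 | Randomised within wards | No |
| Group 1 (SBAR only) v usual care | Not randomised | Yes, 3 hospitals v 1 |
| Groups 1-4 (programme) v usual care | Not randomised | Yes, 3 hospitals v 1 |

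With one control ward, an indicator for that ward is the same variable as the indicator for usual care. Measured patient case-mix can be adjusted for. What remains at ward level cannot be separated from treatment. The intervention wards are meant to cover three hospital types, and one control hospital can match only one of them. This step needs no numerical assumption.

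**3. Size, as an illustration.** Assumptions, none from the document: complication risk p = 30%; between-hospital SD σ of 3 to 5 points (intraclass correlation σ²/[p(1−p)] = 0.0009/0.21 = 0.004 to 0.0025/0.21 = 0.012); patients spread evenly over the three intervention hospitals; no true effect.

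*Hospital alone.* SD of (one hospital minus the mean of three) = σ√(1 + 1/3).

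- σ = 3: 3.46 points; P(|gap| > 5) = 2[1 − Φ(5/3.46)] = 0.149.
- σ = 5: 5.77 points; P(|gap| > 5) = 2[1 − Φ(5/5.77)] = 0.386.
- In the direction of a spurious benefit only, half of these: about 7% to 19%.

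*A nominal 5% patient-level test that ignores hospital.* Sampling variance = p(1−p)(1/n_c + 1/n_i). Total variance adds σ² × 4/3, which is 0.0012 for σ = 3 and 0.00333 for σ = 5. Type I error = 2[1 − Φ(1.96 × sampling SE / total SE)].

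| Contrast | Sampling SE | Total SE (σ = 3; 5) | Type I error (σ = 3; 5) |
|---|---|---|---|
| 80 v 80 | √(0.21 × 0.025) = 0.0725 | 0.0803; 0.0926 | 7.7%; 12.5% |
| 80 v 320 | √(0.21 × 0.015625) = 0.0573 | 0.0669; 0.0813 | 9.4%; 16.7% |

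Recruiting more patients per ward shrinks the sampling term but leaves σ² × 4/3 untouched.

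**4. What the 2007 baseline adds.** It shows usual care before the intervention, and the phrase on reviewing records in each hospital can be read as including the control hospital. The text describes comparison with baseline, not the change in the intervention hospitals minus the change in the control hospital. The populations also differ:

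- The trial requires good cognition, consent, an operated fracture and admission to the surgical ward.
- The baseline takes surgical and orthopaedic admissions and excludes only pathological fracture, polytrauma and elective admission.

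Functional mobility, a primary outcome, is not among the main baseline variables.

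**The case against.** Several points on the other side deserve weight.

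- **The allocation is openly described**, with a practical reason for not randomising SBAR, and the strengths section claims protection only among the three wards. This is fair, but it does not correct the Study design sentence or supply the missing limitation.
- **There is a second source of usual-care data.** A reader might infer that the programme's effect rests on nothing but a concurrent three-against-one comparison. The documents do not support that, because a comparison with the 2007 review is planned. It weakens the charge without answering it, since no control-adjusted change is stated.
- **No test is fixed.** A reader might infer that the trial will declare hospital differences to be intervention effects. Data analysis speaks only of analyses at patient and group level and names no model, which a fuller document may do. The error rates above are conditional on a test that ignores hospital.
- **Question 2a is partly a process evaluation.** The SBAR evaluation section relies on uptake, nurse interviews, observed rounds and record completeness, and describes no comparison with the control ward. Yet question 2a asks about harm, and Study design promises a comparison with usual care.
- **Ward information is useful.** It can support comparison among the three intervention wards, and patient case-mix can be adjusted for against the control. The sentence on correcting for differences therefore needs limiting, not removal.

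**Conclusion.** The point stands for the usual-care contrasts and only for them. The concurrent effects of SBAR and of the programme against usual care are confounded with hospital. The description of that comparison as randomised at patient level is wrong, and the intention-to-treat definition cannot apply to control patients. This follows from the allocation as written, so an analysis plan that is not shown could not change it.

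The size is an illustration. At an assumed 30% risk and a between-hospital SD of 3 to 5 points, hospital alone exceeds the 5-point target in either direction 15% to 39% of the time (7% to 19% as spurious benefit). A test ignoring hospital would have a type I error of about 8% to 13% for 80 v 80 and 9% to 17% for 80 v 320. Other values of risk or SD would move these figures; the confounding itself does not depend on them.

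It would be wrong to conclude that the trial as a whole is not randomised. The card and leaflet contrasts are randomised within wards and estimate effects on top of SBAR.

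**What to change.** 1. In Study design and in the aim, limit the randomised-trial wording to the card and leaflet contrasts among groups 1 to 4. Limit the intention-to-treat sentence in Data analysis to the same groups.
2. Label SBAR and programme versus usual care a non-randomised controlled before-after comparison, and add this to the limitations.
3. For the record-review outcomes (complications and adverse events), analyse that comparison as the change from 2007 in the three intervention hospitals minus the change in the control hospital. Adjust for case-mix, align the baseline and trial populations as far as the records allow (cognition, operated fracture), and show results by ward.
4. State that hospital-specific changes over time remain inseparable from the effect with one control hospital, and draw no confirmatory causal conclusion.
5. In Participating surgical wards, restrict the sentence on correcting for ward differences so that it does not claim to remove differences between the control and intervention wards.

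The cost is wording, one extra model on record reviews already planned, and a weaker claim for the programme. The repair does not reach functional mobility, which the baseline review does not list among its main variables.
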